### Sample size and power calculations

Similar community-based intervention studies using change in symptom-based questionnaires, like the Hospital Anxiety and Depression Scale (HADS) [35–37], have used effect sizes of at least 0.4 when testing treatment as usual groups with limited or no active therapeutic elements, as we propose. Assuming an effect size of 0.4 for the primary endpoint (HADS total score at 20 weeks), with 90% power and 5% significance, an intracluster correlation coefficient of 0.05, and a two-sided hypothesis test with 34 health worker catchment area clusters randomised at a 1:1 allocation ratio, and accounting for 20% attrition, we will need 612 participants (i.e. 306 in each arm). This means that we will need on average 18 participants from each of the 34 health worker catchment areas. A pilot study conducted a nearby Union Council found that these recruitment numbers were feasible and achievable [27], and previous research in the same setting identified a high prevalence of mental health problems in women [38].

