#### Secondary outcome measures

Secondary outcomes include depressive disorder measured by the Primary Health Questionnaire [40–42]; post-traumatic stress disorder (PTSD) symptoms measured by the Post-traumatic stress disorder Check List (PCL-5) [43]; levels of social support measured by the Multi-dimensional Scale of Perceived Social Support (MSPSS) [44]; and levels of functioning as assessed by WHODAS [31]. Costs of health care are measured using the Client Service Receipt Inventory (CSRI) [45]. Self-report wellbeing outcomes are assessed using the Psychological Outcomes Profile Instrument (PSYCHLOPS) [46]. Table 1 indicates the time points for administering each instrument.

**Table 1 Tab1:** Assessment instruments and administered time point

Concept (instrument)	Screening	Baseline assessments	7-week assessment	20-week assessment
Depression and anxiety (Primary outcome)		HADS	HADS	HADS
Functioning	WHODAS		WHODAS	WHODAS
Distress – common mental disorder	GHQ-12			
Depressive disorder		PHQ-9	PHQ-9	PHQ-9
Adverse life events				Section 1 of HTQ Life Events Checklist for Pakistan
Symptoms of post-traumatic Stress Disorder		PCL-5	PCL-5	PCL-5
Perceived social support		MSPSS	MSPSS	MSPSS
Cost of health care		CSRI		CSRI
Self-reported wellbeing		PSYCHLOPS	PSYCHLOPS	PSYCHLOPS

*CSRI* Client Service Receipt Inventory, *GHQ* General Health Questionnaire for common mental disorders, *HADS* Hospital Anxiety and Depression Scale, *HTQ* Harvard Trauma Questionnaire, *MSPSS* Multi-dimensional Scale of Perceived Social Support, *PCL* Post-Traumatic Stress Disorder Check List, *PHQ* Patient Health Questionnaire-9, *PSYCHLOPS* Psychological Outcomes Profile Instrument, *WHODAS* WHO Disability Assessment Schedule for functional impairment

Briefly, the Patient Health Questionnaire-9 (PHQ) is a 9-item instrument measuring the likely presence and severity of depressive disorder against the *Diagnostic and Statistical Manual of Mental Disorders, fourth edition* (DMS-IV) [42]. It uses a 4-point Likert scale where symptom severity is rated over the last 2 weeks from not having the symptom at all, to having it nearly every day. The sum of items gives the total score, with a cut-off of ≥10 as the most accurate for detecting depression [47]. The PHQ has been validated in Urdu [40, 41].

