### Statistical methods

Data will be analysed using SAS 9.3 and SPSS Version 21. Findings will be reported according to the Consolidated Standards of Reporting Trials (CONSORT) guidelines for cRCTs [56]. Primary analyses will be based on the intention-to-treat population and secondary analyses will be based on the per-protocol population. A linear mixed model will be employed for the primary endpoint analysis. The mixed model will have treatment, visit, interaction between treatment and visit as fixed effects, baseline measurement of HADS as covariate, and cluster and subject as random effects. The mean difference between two treatment arms at each visit, together with its 95% confidence interval (CI), will be derived from the mixed model. Covariate-adjusted mixed model of primary endpoint will also be performed by adding prespecified covariates at baseline into the above model. Missing data will be treated as missing at random in the mixed model analysis and no imputation of primary endpoint will be made. To assess the sensitivity of the result to this assumption, the last observation carried forward strategy will be used to compute missing primary endpoints. Subgroup analysis will be performed on the prespecified covariates.

Continuous secondary outcomes will be analysed in a similar way as the primary endpoint analysis. For the analysis of binary secondary outcomes, a generalised mixed model will be employed with treatment, visit, interaction between treatment and visit as fixed effects, baseline measurement as covariate, and cluster and subject as random effect. The odds ratio between two treatment arms at each visit together with its 95% CI will be derived from the generalised mixed model.

All analyses will be described in detail in the finalised and signed statistical analysis plan before unmasking the study.

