#### Economic analysis

Health economic analysis will be conducted to determine the difference in costs and outcomes in the intervention arm as compared to the control arm.

We take a broad public health and societal perspective to assessing economic implications, including all direct cost of health, social, voluntary and private sector services accessed by participants; productivity losses of the participant and caregivers; and informal care and out-of-pocket expenses.

Primary analysis will be of total costs over the 20-week follow-up treatment period. Recognising that cost data are often skewed, the bootstrap technique will be applied. The sampling with replacement from the original observed paired of costs and effects will be employed to maintain the correlation structure between costs and benefits, and bootstrapping sampling will be repeated 1000 times. For each bootstrap sample, an estimate of differential total mean costs and expected mean effectiveness will be calculated. The 95% CIs for the differential estimates will be derived from the 2.5th and 97.5th percentiles [57, 58].

Cost-effectiveness will be assessed by combining costs with the outcome measures including (1) HADS-A and HADS-D scores and (2) WHODAS total score in incremental cost-effectiveness analysis. Repeat resampling from the costs and effectiveness data (bootstrapping) will be used to calculate the probability that each of the treatments is the optimal choice, subject to a range of possible maximum values (ceiling ratio) that a decision-maker might be willing to pay for a unit improvement in HADS-A and HADS-D scores, and WHODAS scores.

The results of the cost-effectiveness will be reported as incremental cost-effectiveness ratios, and acceptability curves which summarise the information contained in a cost-effectiveness plane [59].

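### The economic bootstrap is described as a difference in means with no baseline covariate named, although baseline costs and scores are collected and the HADS analysis is baseline-adjusted

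*Protocol article*

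**What the plan says.** The economic analysis section of the protocol article sets out a procedure.

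- The cost quantity: "Primary analysis will be of total costs over the 20-week follow-up treatment period".
- The resampled unit: "The sampling with replacement from the original observed paired of costs and effects will be employed", repeated 1000 times.
- The statistic per replicate: "For each bootstrap sample, an estimate of differential total mean costs and expected mean effectiveness will be calculated", with percentile limits for the 95% interval.
- The effect terms: "combining costs with the outcome measures including (1) HADS-A and HADS-D scores and (2) WHODAS total score in incremental cost-effectiveness analysis".

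No baseline covariate appears in that section. Two other places bear on it.

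- Table 1 (secondary outcome measures) shows the CSRI, in the row "Cost of health care", at baseline and 20 weeks. It shows HADS at baseline, 7 and 20 weeks, and WHODAS at screening, 7 and 20 weeks.
- The statistical methods section gives the primary mixed model, with "baseline measurement of HADS as covariate". It says continuous secondary outcomes will be handled similarly, and it leaves full detail to a statistical analysis plan that is not at hand.

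**The concern.** A cost-effect pair holds no baseline value, so the plain reading of the bootstrap is a simple difference in means between arms. The main statistical section adjusts HADS, and by extension the continuous secondary outcomes, for baseline. The same HADS and WHODAS data could therefore yield one effect estimate in the efficacy results and another in the ICER.

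Only 34 clusters are randomised, so the arms may differ by chance in baseline distress, functioning or prior service cost. A difference in means keeps the part of that imbalance which persists to 20 weeks, whichever unit the bootstrap resamples. Cost-effectiveness is a stated objective of the trial and lower health costs a stated secondary hypothesis, so the precision of these estimates matters.

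**Working it through.** **Inputs from the protocol article (sample size section):** effect 0.4 SD on HADS total at 20 weeks, 90% power, two-sided 5%, ICC 0.05, 34 clusters (17 per arm), 18 women per cluster, 20% attrition, 612 in total.

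**Assumptions (not in the document):** the baseline-to-follow-up correlation r, taken as 0.3, 0.5 and 0.6 and equal at cluster and individual level; and that the planning ICC also holds at baseline, with 0.01 to 0.10 as the range.

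**1. The plan's own figure.** Individually randomised, the trial needs 132 per arm. The design effect is 1 + 17 × 0.05 = 1.85. Then 132 × 1.85 = 244.2, and 244.2 / 0.80 = 305.25, rounded up to 306 per arm, or 612. The stated figure reproduces.

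**2. Chance baseline difference between arms.** In SD units its SD is √(2 × (ICC + (1 − ICC)/18) / 17).

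| ICC | SD of arm difference | 95% range |
|---|---|---|
| 0.01 | 0.087 | ±0.17 |
| 0.05 | 0.110 | ±0.22 |
| 0.10 | 0.133 | ±0.26 |

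At ICC 0.05: √(2 × (0.05 + 0.0528) / 17) = √0.0121 = 0.110. With 14.4 women analysed per cluster (20% attrition) it is 0.117.

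**3. Carry-over into an unadjusted HADS difference.** This is r × the baseline difference. At ICC 0.05 and 18 per cluster:

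| r | At one SD (r × 0.110) | At the 95% limit (r × 1.96 × 0.110) | 95% limit as share of 0.4 | Variance removed (r²) |
|---|---|---|---|---|
| 0.3 | 0.033 | 0.065 | 16% | 9% |
| 0.5 | 0.055 | 0.108 | 27% | 25% |
| 0.6 | 0.066 | 0.129 | 32% | 36% |

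**4. Simulation check.** There were 4000 trials for each r, with 34 clusters of 14, ICC 0.05 and a true effect of 0.4 SD. Adjusted and unadjusted estimates both averaged about 0.40. Adjustment reduced the SD of the estimate from 0.121 to 0.115 at r = 0.3 and from 0.114 to 0.100 at r = 0.5. The two estimates differed by more than 0.071 SD (r = 0.3) or 0.118 SD (r = 0.5) in 5% of trials, in line with step 3.

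**5. Costs.** The document gives neither a cost SD nor a correlation between baseline and follow-up costs, so no size can be worked out for the incremental cost.

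**The case against.** The strongest reply is that the economic section is silent on adjustment and does not rule it out. A reader might infer that the plan commits to a crude comparison. The document does not say so: an estimate of differential means could come from a regression in each replicate. The statistical methods section points towards baseline adjustment for continuous secondary outcomes, among which costs and WHODAS are listed, and defers detail to the analysis plan. That much stands. But the economic section goes beyond leaving detail open. It fixes the resampled unit, the number of replicates, the statistic and the interval, and the unit it names has no place for a baseline value. A general deferral does not settle which of the two described approaches governs costs, HADS and WHODAS.

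The size can also be called modest, and this stands too. The 16% to 32% figures are 95%-limit values; at one SD the carry-over is about 8% to 16% of the target effect (0.033/0.4 to 0.066/0.4). At r = 0.3 the gain in precision is small.

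A reader might further infer that the lack of a named ICER on HADS total is an error. It is not shown to be one: the list of outcomes is introduced as open-ended, so that is a separate reporting preference.

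**Conclusion.** The point holds as a cheap improvement to the method. On its plain reading the economic section uses a difference in means with no named baseline covariate, while the data for adjustment are collected and the HADS analysis uses its baseline value. The consequences are lost precision, chance imbalance left in the realised estimate, and a possible mismatch between the ICER's effect term and the reported effect.

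For HADS, the carry-over is about 0.03 to 0.07 SD at one SD and 0.065 to 0.13 SD at the 95% limit, against 0.4 SD. Adjustment would remove about 9% to 36% of the variance. These figures rest on assumed correlations of 0.3 to 0.6 and on the planning ICC applying at baseline.

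Two stronger readings are tempting and unsupported. The first is that the economic result would be biased; randomisation makes the difference in means unbiased, and the simulation agrees. The second is that baseline imbalance passes in full into the ICER; only the fraction r of it does. Nothing can be claimed about the size of the effect on incremental cost.

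**What to change.** Add to the economic analysis section that:

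- the baseline values are resampled together with each cost-effect pair;
- in each replicate, the incremental cost comes from a regression of 20-week total cost on arm and baseline CSRI cost;
- in each replicate, the incremental effect comes from a regression of the outcome on arm and the baseline value of that measure (baseline HADS, or screening WHODAS), in line with the statistical methods section.

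The full mixed model need not be refitted 1000 times; a simple baseline-adjusted regression gives the gain. No new data are needed and the extra code is short. The small downside is that missing or skewed baseline costs need a simple rule, which should be written down before unmasking.

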### Ethical considerations

The trial protocol has received ethical approval from the Institute of Psychiatry, Benazir Bhutto Hospital, Rawalpindi, Pakistan and the World Health Organisation Ethical Review Board. The study has also received support from the Swat District Health Department and People’s Primary Healthcare, and from the Psychiatry Department at Saidu Teaching Hospital, Swat.

#### Trial management

Overall trial management is provided by a Project Steering Committee comprised of all senior research and intervention staff, local and international PIs, technical experts, and external advisors who meet fortnightly during trial recruitment and follow-up, and monthly following the completion of endpoint assessments. The Project Steering Committee receives reports from the Trial Management Committee comprised of local research and intervention teams responsible for day-to-day trial conduct. A Trial Advisory Board comprised of persons independent of the trial with expertise in trial management and local culture meets monthly. This board is chiefly responsible for reviewing all adverse reactions and serious adverse events (SAEs) to determine if they are attributable to the trial.

#### Adverse event monitoring

All adverse reactions and SAEs reported spontaneously by the participant, or observed by research or intervention staff, will be recorded. An event is considered a potential SAE if it is an undesirable experience occurring to a participant during the study, whether or not considered related to the research procedure. The chair or a nominated person from the Trial Advisory Board will review SAEs within 48 h, deciding if it is likely related or unrelated to the intervention; and the Trial Advisory Board will review all adverse reactions twice a month. In both instances, the Trial Advisory Board will determine if any appropriate action in respect of ongoing trial conduct is necessary and specify what action this would be (i.e. referral to specialised care). The site PI will inform trial participants and those bodies providing ethical oversight if anything occurs on the basis of which it appears that the disadvantages of participation may be significantly greater than was foreseen.

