### PM+ Group intervention

PM+ is a brief WHO psychological intervention based on evidence of established behavioural techniques for addressing symptoms of common mental health problems in low- and middle-income countries. The manualised intervention involves empirically supported strategies of problem-solving, behavioural activation, accessing social support, and stress management training [23, 26]. Prior to implementation, a period of formative work was undertaken to contextually adapt the intervention and training materials for delivery to women in Swat, Pakistan, and a pilot trial conducted [27].

PM+ Group is an adaptation of the individual PM+ intervention. It was developed through 6 months of formative work, including review by 28 international experts. The group intervention (manual available upon request) involves five weekly sessions each lasting for 3 h, inclusive of breaks. The first session opens with psychoeducation, including information on common reactions to adversity, the rationale for PM+, goal setting, and brief motivational interviewing. Sessions 1 to 4 each introduce a strategy: (1) Managing Stress, (2) Managing Problems, (3) Get Going, Keep Doing (i.e., behavioural activation), and (4) Strengthening Social Support that are applied by participants to problems that they are facing. Each strategy is reviewed in subsequent sessions, with application of strategies between sessions encouraged to enhance learning through repetition. The final session involves a revision of learning, education on preventing relapse, and ends with a culturally appropriate closing ceremony. To enhance accessibility for illiterate individuals the programme is structured around locally relevant and appropriate pictorial materials and adopts a narrative format to support engagement and individual disclosure of personal difficulties which can be more difficult in a group format. Specifically, a case example of a woman experiencing common practical and emotional problems is shared each week, with participants following her progress through PM+ Group.

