LHWs provide logistical support to PM+ Group facilitators, including the provision of a room in her house in which to conduct sessions, and convening sessions with participants from her catchment area. LHWs do not deliver the intervention, this is done by female facilitators. The PM+ Group female facilitators are recruited from Swat and have a minimum of 16 years of education and no previous experience in providing mental health care. Facilitators received 7 days of intervention training, delivered by the master trainer ([name]) and supported by three in-country supervisors (PA, HN, AM). Prior to attending training in PM+, facilitators underwent a half-day orientation to Psychological First Aid (Urdu version) [28] to sensitise them on how to appropriately respond to current crises a woman may be experiencing. Intervention training included education on adversity and its impact upon mental health, basic counselling skills, delivering PM+, skills in group facilitation, and facilitator self-care. An additional half-day security training for working in unstable settings was also provided. To build confidence and competence following training, all facilitators delivered one practice group each at an accelerated rate (five sessions in 2 weeks), with participants living outside the trial area, under intensive supervision. After conclusion of practice groups all facilitators underwent competency assessments prior to delivery of PM+ Group to cRCT participants. In case of insufficient competency additional targeted training is provided and competency assessments readministered. A co-facilitator who occupies a support role (e.g., providing child care and supporting LHWs with logistical arrangements) supports facilitators in each group. Co-facilitators participated in a half-day orientation to their role delivered by the facilitators.

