Consistent with an apprenticeship model [16], protocol adherence is ensured through weekly supervision of the facilitators provided by three trained PM+ Group supervisors based in Islamabad; and fortnightly supervision of the supervisors by the master trainer. Involving all facilitators in a group, supervision lasts 2 to 3 h, conducted via Skype. Supervision entails reviewing the progress of groups including case management of participants and additional refresher training on intervention components and group facilitation skills through role play. The supervisors are in turn provided with supervision by the master trainer, conducted fortnightly via Skype and also lasting 2 to 3 h. Intervention fidelity is monitored through independent observations of 15% of randomly selected sessions of each facilitator against tailored checklists. These fidelity checks are conducted by persons trained in PM+ Group but not acting as study facilitators or supervisors.

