### Enhanced usual care (EUC)

Control and intervention arm participants will continue to receive routine LHW visits on an individual basis. The care that they receive is considered to be EUC as usual care for common mental disorders in primary care in Pakistan typically involves no or placebo care leaving the majority of cases of distress undetected and unsupported. EUC will comprise:Providing LHWs and primary health care providers with training in the detection and management of mental health care needs, and referral pathwaysProviding feedback to all participants about their assessment resultsProviding all participants with information about the options for seeking appropriate care for distress (i.e. through their LHW, the BHU, or the tertiary health care centre)

Both arms have unrestricted access to EUC through their routine health providers. The intensity of services received in both arms will be measured at 20 weeks as part of the economic evaluation (see below).

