**Fig. 2 Fig2:**
[figure not shown]
Schedule of enrolment, interventions, and assessments

If a catchment area is allocated to the intervention arm, the LHW contacts all participants within her cluster to schedule an initial meeting to introduce the participant to the intervention facilitator. This is a necessary engagement step in this setting where service uptake is dependent upon a trusted relationship with the service provider. If allocated to the control arm the LHW continues routine visits to women in her catchment area.

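### Adverse events are recorded only if volunteered or noticed by staff, and one of the two staff groups meets PM+ women only, so any tabulation by arm is open to unequal ascertainment

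*Protocol article*

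**What the plan says.** The Adverse event monitoring section gives the capture rule: "All adverse reactions and SAEs reported spontaneously by the participant, or observed by research or intervention staff, will be recorded". It names two routes, spontaneous report and staff observation. The net is wide, because an undesirable experience counts as a potential SAE whether or not it is thought related to the research. The Trial Advisory Board decides relatedness and whether trial conduct needs action. The site PI must inform participants and the ethics bodies if the disadvantages of taking part look significantly greater than foreseen.

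The arms differ in who is there to observe:

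- **PM+ arm.** The intervention "involves five weekly sessions each lasting for 3 h, inclusive of breaks" (PM+ Group intervention section). Before that, the LHW contacts participants "to schedule an initial meeting to introduce the participant to the intervention facilitator" (Randomisation section, text after Fig. 2). A second staff member is present: "A co-facilitator who occupies a support role (e.g., providing child care and supporting LHWs with logistical arrangements) supports facilitators in each group". Weekly supervision adds a further look at each woman: "Supervision entails reviewing the progress of groups including case management of participants".
- **Control arm.** "If allocated to the control arm the LHW continues routine visits to women in her catchment area" (same part of the Randomisation section). No contact with intervention staff is scheduled.
- **Both arms.** Researchers assess every woman at 7 and 20 weeks. Routine LHW visits also go on in both arms: "Control and intervention arm participants will continue to receive routine LHW visits on an individual basis" (Enhanced usual care section).

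**The concern.** Under a passive rule, an event enters the record only if a woman volunteers it or a staff member is there to notice it. One of the two named staff groups exists for PM+ women only. With identical true event rates, the PM+ arm would be expected to show more recorded events, because control events are more often missed.

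Two uses of the data are exposed. The first is any table of adverse events by arm. The second is any background rate that the Board or the site PI has in mind when asking whether an event is related to PM+, or whether taking part has proved worse than foreseen. With so wide a definition of a potential SAE, much ordinary illness and misfortune is eligible, and how much of it is recorded depends on who is present. No later analysis can recover control-arm events that were never collected.

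**Working it through.** The article gives no adverse event rate, no capture probability and no planned safety test, so there is no figure of the plan's own to reproduce. The check counts scheduled contacts and then shows what unequal contact could do under stated assumptions.

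**Contacts after baseline, from the article**

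- PM+: 1 introduction + 5 sessions + 2 assessments = 8. Session time is 5 × 3 h = 15 h.
- Control: 2 assessments, and 0 h with intervention staff.

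**Assumptions, not in the article**

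- True event rates are equal in the two arms.
- Each contact after an event captures it independently with probability p, taken as 10% or 20%.
- An event followed by k contacts is therefore captured with probability 1 − (1 − p)^k.

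**Case A: the event is present before the first contact** (k = 8 v 2)

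- p = 0.1: 1 − 0.9^8 = 0.570 v 1 − 0.9^2 = 0.190, ratio 3.0.
- p = 0.2: 1 − 0.8^8 = 0.832 v 1 − 0.8^2 = 0.360, ratio 2.3.

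**Case B: events spread evenly over 20 weeks.** Assume the introduction at week 1, sessions at weeks 2 to 6, and assessments at weeks 7 and 20. In the PM+ arm an event in each of weeks 1 to 7 has 8, 7, 6, 5, 4, 3 and 2 contacts still to come. In the control arm it has 2 throughout that time. From week 7 to week 20 (13 weeks) each arm has 1.

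- p = 0.1, PM+: (0.570 + 0.522 + 0.469 + 0.410 + 0.344 + 0.271 + 0.190 + 13 × 0.1) / 20 = 0.204. Control: (7 × 0.190 + 13 × 0.1) / 20 = 0.132. Ratio 1.55.
- p = 0.2, PM+: (0.832 + 0.790 + 0.738 + 0.672 + 0.590 + 0.488 + 0.360 + 13 × 0.2) / 20 = 0.354. Control: (7 × 0.360 + 13 × 0.2) / 20 = 0.256. Ratio 1.38.

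**Case B with an earlier start.** With the introduction at week 0.5 and sessions at weeks 1 to 5, the same calculation gives ratios of 1.41 (p = 0.1) and 1.29 (p = 0.2).

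Case B is the fairer picture, since 13 of the 20 weeks fall after the sessions have ended and carry no contact imbalance. Case A is the upper end.

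**In counts.** At an assumed true risk of 5% and 306 women per arm there are 306 × 0.05 = 15.3 true events per arm. Case B with the later start records about 15.3 × 0.132 = 2.0 control v 15.3 × 0.204 = 3.1 PM+ events at p = 0.1. At p = 0.2 it records 15.3 × 0.256 = 3.9 v 15.3 × 0.354 = 5.4. Under these assumptions most events are missed in both arms, and more of them among controls.

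**Limits of the model.** It gives a 3-hour group session with two staff the same capture probability as a one-to-one assessment, which could err in either direction. It ignores events volunteered between contacts; if these were equally common in both arms, the ratio would move toward 1.

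**The case against.** The strongest reply is that the plan never sets out to compare safety between arms. A reader might infer that a planned between-arm comparison is biased, or that the Board would act on arm counts. The article supports neither. No such comparison appears in the objectives, outcomes or statistical methods, and the Board reviews events case by case. Closer observation of PM+ women also helps to find harm caused by PM+. This part of the reply stands. What remains is that any table by arm, and any background rate behind a relatedness judgement, would rest on unequal capture.

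A second reply is that both arms are asked about events. At 20 weeks the Harvard Trauma Questionnaire section and the life-events measure ask about events since enrolment, and the CSRI measures service use. It would be wrong to say that no event question is common to the arms. These instruments are not tied to the adverse event record, however, and there is no equivalent at 7 weeks.

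A reader might also infer that worse distress in controls would go unseen. It would not: HADS, PHQ-9 and PCL-5 are given to both arms at 7 and 20 weeks, and all participants receive feedback on their assessment results.

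Third, LHWs visit both arms and are trained in detection under enhanced usual care. They are not clearly among the research or intervention staff named in the rule. If they do count, contact is still unequal, because LHWs in PM+ clusters also convene and host the sessions.

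Finally, an unseen SAP or full protocol may add safety tables. Neither can make good events that the stated rule did not collect.

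**Conclusion.** The point holds in a limited form. The capture rule is stated and passive, and one of its two observing groups sees only one arm. Any tabulation of adverse events by arm is therefore open to differential ascertainment, most likely under-recording control events.

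The direction is well supported; the size is illustrative. The spurious ratio is roughly 1.3 to 1.6 with 10% to 20% capture per contact, evenly spread events and the session timings assumed above. A ratio of 2.3 to 3.0 should not be quoted as the expected bias, since it applies only to events that precede every contact. The primary efficacy analysis and the sample size are not touched. This is a cheap improvement worth making, not a flaw that threatens the trial's main conclusion.

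**What to change.** At the 7- and 20-week assessments, have the masked researcher ask every woman the same short structured questions on adverse events since the last assessment. Put them after the outcome scales, so that HADS stays first and any unmasking answer comes too late to affect it. The article already applies this logic by placing the CSRI last at 20 weeks.

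Base any tabulation by arm on these answers alone. List events noticed in sessions or volunteered at other times separately, marked as such, and leave the Board's individual review of every event unchanged. If some assessments have already been done without the questions, limit the tabulation to the assessments at which they were asked and say so.

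The cost is a few minutes per existing visit, one form, more events to process, and a small unmasking risk that late placement limits. The gain is equal solicited capture in both arms, with an expected ratio of 1.0 under equal true risk, and better detection of harm among control women.
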